**14. EXPERIENCE**

The faculty investigator has extensive research working with this population and is considered an international expert in the field of ADHD/LD. Currently, she holds a Canada Research Chair (Tier 1) in Special Education at OISE/University of Toronto, where she is a Professor in Special Education and in Psychiatry; she is also a senior scientist in the Neurosciences and Mental Health Research program at the Hospital for Sick Children. She supervised the doctoral student, [name], who was listed as Primary Investigator on the original protocol for this study, approved by the university Research Ethics Board.

[name], who has completed his doctoral research and expects to defend in his thesis in a couple of months time, will then become [name] Doctoral Student. He will supervise the neuroimaging component of the project and assist [name] in supervising the behavioral components of the project. He has obtained various international EEG certifications from basic and advanced EGI trainings (2006, 2007) as well as bootcamps (2008) from renowned ERP researchers, such as [name]. These, in combination with more than 3 years of experience with the EEG system at the University of Toronto demonstrate sufficient expertise with the various procedures of conducting EEG research. [name] has played a major role in designing the modified protocol and in writing the CIHR grant that supports this ongoing project.

**15. RECRUITMENT**

Participants will be recruited through the Accessibility Services from several universities and colleges in and around Toronto, such as the University of Toronto, York University, Ryerson, George Brown, and Humber. Students will be notified about an information session will be held on campus describing the Cogmed Working Memory Training Program as well as the proposed research study. At that time, students will be given the opportunity to sign-up to participate if they are interested.

**16. COMPENSATION**

(a) Will participants receive compensation for participation?

**Financial** Yes  No

In-kind Yes  No

Other Yes  No

(b) If **Yes**, please provide details.

Participants will receive $40 for the first visit, $80 for the second visit, and $80 for the last, follow-up visit. The comparison group will receive $60 for their visit.

(c) Where there is a withdrawal clause in the research procedure, if participants choose to withdraw, how will you deal with compensation?

Participants will be paid for their presence at the testing lab, even if they withdraw during that testing session.

| **SECTION C –DESCRIPTION OF THE RISKS AND BENEFITS OF THE PROPOSED RESEARCH** |
| --- |

**17. POSSIBLE RISKS**

1. Indicate if the participants as individuals or as part of an identifiable group or community might experience any of the following risks by being part of this research project:

(a) Physical risks (including any bodily contact or administration of any substance)? Yes  No

(b) Psychological/emotional risks (feeling uncomfortable, embarrassed, anxious or upset)? Yes  No

(c) Social risks (including possible loss of status, privacy and/or reputation)? Yes   No

(d) Is there any deception involved? (See Debriefing, #21) Yes   No

2. If you answered **Yes** to any of the above, please explain the risks, and describe how they will be managed and/or minimized.

Participation in the proposed research project will entail a substantial time commitment on the part of the college students. At times, they may feel a little overwhelmed or anxious. Prior to beginning the intervention, the principal investigator will be conducting an information session on campus whereby participants will be informed of what they can expect should they choose to participate. In addition Cogmed coaches, who are registered clinical psychologists, will be available to students throughout the duration of the study for extra support. These coaches will call the students weekly to check-in and see how they are managing. Calls will be made for all three groups who are involved in the training.

The neuroimaging tasks may take 60 minutes per session during which the participants are encouraged to restrict their movements. This extended time period of sitting still may be mildly uncomfortable. To minimize this discomfort, measures have been taken to allow for sufficient breaks during the testing procedure. It is also essential for the adequate recording of our measures that participants are in a comfortable and relaxed physical position as well as mental state. Therefore, at least once every 10 minutes there will be a scheduled break of at least 10 minutes long. Furthermore, the tasks will be programmed in a manner allowing for optional breaks at the participant’s convenience, or the researchers discretion, by simply pressing the spacebar.

The EGI sensor nets used for the brain measurements are amongst the most easy-to-apply, user-friendly and widely used methods of doing brain imaging. Due to its safe application procedures and noninvasive ways of measurement, the method is even used in infant research (Leppanen et al., 2007).

**18. POSSIBLE BENEFITS**

Discuss any potential direct benefits to the participants from their involvement in the project. Comment on the (potential) benefits to the scientific/scholarly community or society that would justify involvement of participants in this study.

Participants may gain direct benefit from participating in the project in terms of improvement in their working memory abilities and a possible decrease in their ADHD symptoms. Also, findings from this study will contribute to the growing data-base on the efficacy of working memory training in individuals with ADHD/LD. This information will in turn help other individuals with ADHD to understand the effectiveness and utility of working memory training. Upon request, an image of the participant’s brain activity will be mailed to the participant.

| **SECTION D – THE INFORMED CONSENT PROCESS** |
| --- |

**19. THE CONSENT PROCESS**

Describe the process that the investigator(s) will be using to obtain informed consent. Please include the experience of the team member with this participant population and/or training that this person will receive prior to recruitment. If there will be no written consent form, please explain (e.g. discipline, cultural appropriateness, etc.). Please note, it is the quality of the consent, not the format that is important. If the research involves extraction or collection of personal information from a data subject, please describe how consent from the individuals or authorization from the custodian will be obtained.

For information about the required elements in the information letter and consent form, please refer to [**http://www.research.utoronto.ca/ethics/eh_best.html**](http://www.research.utoronto.ca/ethics/eh_best.html)**.**

**Where applicable, please attach a copy of the Information Letter/Consent Form, the content of any telephone script, letters of administrative consent or authorization and/or any other material which will be used in the informed consent process.**

The primary and faculty investigators will be holding an information session on campus, where students will have the opportunity to ask questions. Those who are interested will be given the opportunity to sign up at that point and the consent procedures will be explained to them face-to-face. Should they choose to participate, written consent will be obtained (please see attached consent form for further information). A second session will also be held, for those individuals who may wish to sign up later.

**20. CONSENT BY AN AUTHORIZED PARTY**

If the participants are children, or are not competent to consent, describe the proposed alternate source of consent, including any permission/information letter to be provided to the person(s) providing the alternate consent as well as the assent process for participants.

N/A

**21. DEBRIEFING**

(a) If deception will be used in the research study, please explain what information/feedback will be provided to participants after participation in the project.

**Please provide a copy of the written debriefing form, if applicable.**

N/A

(b) How will participants be informed of study results?

Upon completing the study JVS psychologists will provide individual feedback on participants’ individual performance. Also, after the study has been completed, participants will be provided with a summary of the major findings from the study.

**22. PARTICIPANT WITHDRAWAL**

(a) Where applicable, please describe how the participants will be informed of their right to withdraw from the project. Outline the procedures which will be followed to allow them to exercise this right.

When written consent is obtained from the participants, they will be informed verbally about their right to withdraw from the project. Permission will also be requested to administer post-tests at the time of withdrawal. Should participants choose to exercise this right, they can contact [name], [name] administrative assistant (who is not involved in the project) or [name] (Project coordinator), either by phone or e-mail.

(b) Indicate what will be done with the participant’s data and any consequences which withdrawal may have on the participant.

If participants choose to withdraw at any point during the intervention, there will be no consequences. Their data will be kept in a filing cabinet under lock and key. Given that this is a randomized controlled trial, we aim to use an Intent-to-Treat with Last Observation Carried Forward approach (ITT-LOCF) in analyzing the data. Thus we will request permission to use the existing data from any participant who withdraws prematurely.

(c) If participants will not have the right to withdraw from the project at all, or beyond a certain point, please explain.

N/A

| **SECTION E –CONFIDENTIALITY AND PRIVACY** |
| --- |

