WM capacity has generally been thought to be a fixed trait, but recent studies have suggested that it can be improved by intensive and adaptive computerized training ([10](#_ENREF_10)). This intervention approach has been evaluated in children and adolescents with ADHD, older adults, and adult stroke patients and shown promising results ([11-14](#_ENREF_11)). Subjects not only improved on the trained WM tasks, but some of the studies suggest that improvements may generalize to non-trained WM activities, complex reasoning tasks, academic functioning, and behavioral symptoms of ADHD or working memory failure ([11](#_ENREF_11), [15](#_ENREF_15)). Moreover, brain imaging studies have provided converging evidence of training-related improvements in working memory: specifically increased activation has been found in cortical regions implicated in working memory ([14](#_ENREF_14), [16](#_ENREF_16), [17](#_ENREF_17)). However, no studies to date have investigated whether WM capacity can be improved in a population of young adults with ADHD/LD enrolled in post-secondary education programs. Nor have the results been replicated or elaborated upon using different imaging methodologies, like EEG (Electroencephalography), which is able to capture the millisecond time parameters of cognitive processing and so may provide new insights into the neural mechanism of WM and effects of WM training.

The overall objective of the current study is to determine the effectiveness of WM training, as administered by community-based psychologists licensed to provide this training, for college students with ADHD/LD. Specific objectives are to determine whether; i) high-intensity computerized WM training enhances WM capacity in college students with ADHD/LD, using behavioural as well as neuroimaging indices of change; ii) lower-intensity training would also result in improvements in WM; iii) WM training normalizes WM, as compared to typically developing peers (i.e., a healthy comparison group of college students); iv) improvements in WM will generalize to secondary outcome tasks, such as inhibitory control and planning; v) WM training will also ameliorate ADHD symptoms of inattention and hyperactivity; and vi) improvements will be sustained for at least a few months after completing the training.

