The study uses a randomized controlled design in which participants are randomly assigned to one of three groups: standard-length version of high-intensity WM training, a novel shorter version of the high-intensity WM training, or a wait-list control group. The standard-length WM training group will undergo 25 training sessions for 30 min/day, 5 days a week for 5 weeks and receive weekly phone calls from a cogmed coach to review progress and adjust the training as needed; the group assigned to the shorter version of the high-intensity training will also undergo 25 training sessions but for just 15 min/day, 5 days per week for 5 weeks and also receive the same type of weekly phone calls from a cogmed coach; and the wait-list group will not undergo any WM training during the 5 week period but will receive weekly phone calls from a member of the research team to review progress and advice on time management, organization, and mnemonic strategies. All groups will undergo pre testing, testing three weeks following completion of training and again at three-month follow-up. The wait-list group will be offered the cogmed training after the follow-up assessment. We will also recruit a group of healthy age- and gender-matched peers who will be assessed once and will not undergo WM training; this comparison group allows us to determine initial group differences in behavioral and neural indices of WM and whether WM training normalizes these indices in the ADHD groups.

*Diagnostic screening measures* (Baseline assessment only for AHD/LD and healthy controls).

All participants must have received a prior diagnosis of ADHD/LD to register with the college/university Student Disability Services. Since there is no standardized assessment used by Student Disability Services, we will administer a brief interview and standardized rating scales and screening tests to quantify the current symptoms of ADHD, and other clinical problems such as mood and stress levels.

*Adult ADHD Self-Report Scale* (ASRS v1.1) is a reliable and valid scale for evaluating ADHD in adults ([20](#_ENREF_20), [21](#_ENREF_21)). The ASRS v1.1 is an instrument consisting of eighteen questions based on the criteria used for diagnosing ADHD in adults using DSM-IV-TR criteria. Questions focus on how often ADHD symptoms occur (0=never, 1=rarely, 2=sometimes, 3=often, 4=very often). Scores for each item are added to calculate a total score.

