***Neuroimaging Outcome Measures:***

Three well-validated measures of working memory and related processes will be administered in the EEG lab at OISE, adjacent to the cognitive lab where the behavioral measures are administered.

Go-nogo task (response inhibition)

The subject is shown sequences of letters and instructed to press a button whenever a letter shows up on the screen, but to withhold a response whenever a letter occurs twice in a row. This task will take 8 minutes and is adapted from Garavan, Ross, & Stein (1999).

Delayed Working memory task (working memory)

The subject is shown sequences of either 2 (low load) or 4 (high load) shapes. After a delay period of two seconds, a probe appears and the participant needs to respond by pressing a button whether the probe stimulus was part of the sequence shown before or not. This task will take 16 minutes and is adapted from Haenschell et al., (2007).

Selective Working memory task (selective attention + working memory)

The subject is shown an array of small colored squares to different parts of their visual field. This memory array will consist of either 2 (low load), 4 (high load), or 2 (low load + 2 ‘distractor’ circle) items. After a delay, a test-array is shown and the participant is to respond whether the test-array matched the memory array. This task will take 24 minutes and is adapted from Vogel, McCollough, & Machizawa (2005).

*Imaging equipment*

EEG (Electroencephalography) will be recorded using a 128-channel Geodesic Sensor Net (Tucker, 1993). The net consists out of sponges which contain sensors which allow the measurement of brain activity on the surface of the head.

The basic approach to tests the effects of the training program will be to use repeated measures ANOVA. Separate analyses will be conducted for the primary, secondary and tertiary outcome measures.

For the imaging, raw EEG will be sampled at 500 Hz, using EGI software (Electrical Geodesic, Inc., Eugene, OR) and further processed using EGI software (Electrical Geodesics, Inc., Eugene, OR) after which ERP (Event Related Potential: averaged brainwaves) measures will be created and analyzed in SPSS. Repeated measures ANOVA’s will be used to compare levels of brain activity in various regions before and after training.

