**13. PARTICIPANTS OR DATA SUBJECTS**

The sample will include college students with ADHD and/or Learning Disabilities attending the University of Toronto, York University, Humber, Ryerson, or George Brown. The estimated sample size is 160 participants (40 in experimental, 40 in low intensity, 40 in waitlist, and 40 normal healthy controls). Participants will be of no relationship to the investigators. Those who participate in the study must be enrolled as full time students. All participants must have received a previous diagnosis of ADHD and/or a Learning Disability. Exclusionary criteria will include uncorrected sensory impairment, evidence of a neurological dysfunction or a history of psychosis. Personal information, and checks on eligibility, will be obtained directly from the participants during the intake procedures which are appended to this proposal. Ethics approval will be sought for institutions other than the University of Toronto in accordance with those institutions’ policies and procedures.

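### Carrying the last score forward enters zero change from post-test to three months for anyone lost in between, which biases the durability question (objective vi) whenever there is dropout and a true change

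*Protocol*

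**What the plan says.** Four parts of the protocol bear on this.

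- **Missing data.** Section 22(b), on the data of participants who withdraw, states "we aim to use an Intent-to-Treat with Last Observation Carried Forward approach (ITT-LOCF) in analyzing the data" and continues "Thus we will request permission to use the existing data from any participant who withdraws prematurely". The protocol contains no other missing-data method, no sensitivity analysis and no dropout allowance.
- **Tests on withdrawal.** Section 22(a) adds "Permission will also be requested to administer post-tests at the time of withdrawal".
- **The question and the schedule.** Objective vi in section 11 asks whether "improvements will be sustained for at least a few months after completing the training". The Study Design part of section 12 sets the visits: "All groups will undergo pre testing, testing three weeks following completion of training and again at three-month follow-up".
- **Model.** At the end of section 12, under the neuroimaging measures: "The basic approach to tests the effects of the training program will be to use repeated measures ANOVA". The next sentence applies this to the primary, secondary and tertiary outcomes.

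**The concern.** Objective vi is about the change between the post-test and the three-month visit. Last observation carried forward sets that change to zero for everyone who has a post-test and misses the last visit. For those people the method supplies the answer that the trial is meant to find.

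Two further effects follow from the same rule. A participant lost before the post-test who has only a baseline score is recorded as having gained nothing, not even the practice gain from repeating a test. If the arms lose different fractions before the post-test, that alone moves the randomised contrast. And if a score from a test on the day of withdrawal is the one carried forward, it fills visits that were meant to fall later.

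At stake are the claim that any benefit lasts and, where early dropout is unequal, the size of the benefit itself.

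**Working it through.** **Inputs.** From the protocol: three randomised arms of 40 (section 13); 5 weeks of training, a post-test three weeks after it, and a three-month follow-up (section 12). The protocol gives no dropout rate, effect size, SD or power calculation, so there is no figure of its own to reproduce. All values below are assumptions, in SD units.

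**1. General form within an arm.** Let p0 be the share lost before the post-test (baseline carried), p1 the share lost between post-test and follow-up (post-test carried), g the true mean gain at post-test and f the true mean gain at follow-up. Assume that those lost would have followed the same average course as those who stay.

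- LOCF gain at post-test = (1 − p0)·g
- LOCF gain at follow-up = (1 − p0 − p1)·f + p1·g
- LOCF change = (1 − p0 − p1)·(f − g)

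The true change is f − g. LOCF multiplies it by one minus the fraction lost. The shrinkage is toward zero, and it has no effect if p0 + p1 = 0 or f = g.

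**2. Late loss only.** Effect against wait-list 0.50 at post-test, p0 = 0.

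| Lost after post-test | True 0.25 at three months (halved) | True 0 at three months (gone) |
|---|---|---|
| 10% | 0.9×0.25 + 0.1×0.50 = 0.275 | 0.1×0.50 = 0.05 |
| 20% | 0.8×0.25 + 0.2×0.50 = 0.30 | 0.2×0.50 = 0.10 |
| 30% | 0.7×0.25 + 0.3×0.50 = 0.325 | 0.3×0.50 = 0.15 |

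In the halved case, apparent retention is 55%, 60% and 65% against a true 50%.

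**3. Early loss only.** Retest gain r = 0.3 in all arms, training effect d = 0.5, 25% lost in training and 10% in wait-list, no training benefit in dropouts, baseline carried.

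- LOCF contrast: 0.75×(0.3 + 0.5) − 0.90×0.3 = 0.60 − 0.27 = 0.33
- True contrast as randomised: (0.75×0.8 + 0.25×0.3) − 0.3 = 0.375
- With d = 0: 0.75×0.3 − 0.90×0.3 = −0.045 against a true 0

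Under these assumptions the bias is −r × (training loss − wait-list loss) = −0.3×0.15 = −0.045 in both cases. If the two dropout rates are swapped, it becomes +0.045.

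**4. Early and late loss together.** As in step 3, with the effect halving to 0.25, a stable retest gain, and a further share of the training arm lost after the post-test. The true effect at three months is 0.75×0.25 = 0.1875.

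- 10% late loss: 0.65×0.55 + 0.10×0.80 − 0.27 = 0.1675 (too low)
- 20%: 0.55×0.55 + 0.20×0.80 − 0.27 = 0.1925 (almost right)
- 30%: 0.45×0.55 + 0.30×0.80 − 0.27 = 0.2175 (too high)

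The level at three months has no fixed direction of bias. The change still does: from the LOCF post-test value of 0.33 it is −0.1625, −0.1375 and −0.1125, against a true 0.1875 − 0.375 = −0.1875.

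**5. False-positive rate at three months.** Simulation with 40 per arm, 5000 runs, a 0.6 SD post-test gain that is wholly lost by three months, correlation 0.6 between visits, and equal dropout completely at random after the post-test. The test compares change from baseline between two arms at nominal 5%. LOCF rejects in 5.3%, 9.0% and 13.8% of runs for 10%, 20% and 30% loss. Observed scores only reject in 4.8%, 4.9% and 4.9%. The 5.3% is within simulation error of 5% (standard error √(0.05×0.95/5000) = 0.3 points).

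**6. Timing.** The post-test falls 5 + 3 = 8 weeks after training starts. Someone who withdraws and is tested at, say, week 2 would, if that score is carried forward, have a score taken 8 − 2 = 6 weeks early entered as the post-test, and the same score entered again at three months.

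**The case against.** The case against has several fair parts.

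- **The bias is conditional.** It is nil if nobody is lost or nothing changes between the visits, and no dropout rate is given. Section 16 pays $80 for each of the two later visits against $40 for the first, which should help retention. A reader might infer that LOCF makes objective vi unanswerable without bias; the protocol does not support that.
- **Direction.** A reader might infer that LOCF always inflates the three-month benefit. Step 4 shows that it does not. Only the change between visits is pulled consistently one way.
- **Unequal dropout is assumed.** All arms receive weekly calls and the visit payments do not differ by arm. Against that, sections 17 and F expect the training burden to weigh on students, and the wait-list is offered training only after follow-up. Unequal loss is plausible but not shown.
- **Withdrawal-day tests.** Section 22 does not say that such a test becomes the scheduled score, so the timing point is conditional. Nor do steps 3 and 6 add up for one person: early dropouts carry either a baseline or a withdrawal-day score.
- **Size.** With 40 per arm, the unadjusted standard error of a two-arm difference is √(2/40) = 0.22 SD, so a bias of 0.05 is about a quarter of it. That is modest, though step 5 shows it can matter if the effect fades completely.
- **Standard errors.** A claim that every error bar is wrong goes too far. An outcome without missing scores is unaffected.
- **Status of the text.** This is an ethics form, the wording is an aim, and an unseen analysis plan may add analyses. Even so, the protocol names this method and no other.

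These points limit the size and reach of the concern. None makes LOCF a suitable method for a durability question.

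**Conclusion.** The point holds in limited form. LOCF shrinks the estimated post-test to three-month change in an arm by the fraction of that arm lost, and so leans toward a finding of maintenance on objective vi whenever there is both dropout and a true change. The exact factor assumes that those lost would on average have changed as the others did.

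The benefit level at post-test or at three months may be biased either way. If withdrawal-day scores are carried forward, assessment times are mixed as well.

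The size cannot be fixed from the protocol. On the assumed inputs it is 0.025 to 0.075 SD for an effect of 0.50 SD that halves with 10–30% late loss, and 0.05 to 0.15 SD if the effect disappears.

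**What to change.** - **Section 22(b):** replace the LOCF statement with an analysis of all randomised participants as allocated, by a likelihood-based mixed model for repeated measures (arm by visit, adjusted for baseline) on all observed scheduled scores, with nothing carried forward. Add a sensitivity analysis for data not missing at random.
- **Section 12:** amend the repeated measures ANOVA sentence to name the same model. Otherwise the two sections would contradict each other.
- **Section 22(a):** ask participants who stop training but have not refused further contact to attend the post-test and follow-up visits already scheduled. Record any withdrawal-day test at its actual date, and do not use it as the scheduled visit score.

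The visit schedule itself does not need to change for this.

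The cost is a short ethics amendment and slightly more analysis work, with no extra participants and no visits beyond those planned. The mixed model relies on data being missing at random, which the sensitivity analysis probes. The change is best made before recruitment under the amended protocol, because scheduled scores that were never collected cannot be recovered later.
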